### Sample size

The sample size of the trial was derived on the basis of the null hypothesis that the true cure rate was 90% in each group compared with an alternative, unacceptably low, cure rate of 70%; assessment of power at the final analysis given this sample size is discussed later. For a single stratum within a single randomly assigned group, given 90% power and one-sided alpha of 0.05, and 5% loss to follow-up by EOT + 12, 39 patients would be required per group to exclude the cure rate being lower than 70% based on a single-group test. There are 14 groups and two genotype strata, giving a total sample size of 1092 patients (39*14*2). For final comparisons at trial closure, the null hypothesis is that all groups will achieve the more than 90% cure target and be included in the final analysis. There will then be 546 per group for the regimen comparison (non-inferiority; comparing the two WHO-recommended drug regimens against each other), 156 in the control group and 312 per intervention group for the strategy comparison (non-inferiority; comparing each of the three treatment-shortening strategies versus the licensed 12-week control duration), and 468 per group for the ribavirin comparison (superiority; comparing each treatment-shortening strategy with and without ribavirin). The total sample size is fixed at 1092 patients; if individual groups are stopped early, any subsequent patients will be randomly assigned to open groups where possible (depending on the delay between randomisation, identification of primary endpoints and interim analyses), so numbers in each fully recruited group may be higher. This is appropriate in a pragmatic trial, where the goal is to maximise information gained about many different strategic approaches to treatment rather than to minimise sample size per se.

The choice of the non-inferiority margin was based on clinical judgement and the size of margins used in other trials of anti-infectives with relatively low failure rates such as community-acquired pneumonia [30]. In particular, a smaller 5% margin is chosen for the drug comparisons because in practice they are likely to have similar advantages and disadvantages. In contrast, the different drug-sparing strategies have a variety of different advantages and disadvantages (in terms of additional visits vs. less drug vs. different drugs vs. weekends off; Table 1) which could be differentially balanced against overall cure rates, particularly considering impact on health-care provision (e.g., through directly supervised therapy). Thus, a greater non-inferiority margin (here 10%) is relevant to drug-shortening because the potential benefit in terms of numbers treated for the same fixed budget is much greater. Regulatory guidance recommends that non-inferiority margins be chosen to ensure that the difference between an intervention and the active control (here 12 weeks’ duration) would not exceed that between the active control group and a hypothetical placebo (or other standard control group, here the previous standard of care of 12–48 weeks of PEG-IFN) [30]. As cure rates with 12–48 weeks of PEG-IFN were about 70% in genotype 6 [31], with similar or lower cure rates in other genotypes, and as we expect more than 90% SVR12 in all groups, our non-inferiority margins of both 5% for the regimen comparison and 10% for the strategy comparison would ensure this.

From initial power calculations based on all 14 randomly assigned groups, assuming that the overall cure rate is 95%, the fixed total sample size of 1092 patients above provides 97% power to demonstrate non-inferiority between drug regimens based on a 5% margin and 96% power to demonstrate non-inferiority between shortening strategies based on a 10% margin, both with one-sided alpha of 0.05. For superiority comparisons (conducted for ribavirin and any comparison that meets non-inferiority above) and two-sided alpha of 0.05, these numbers provide more than 90% power to detect absolute differences in SVR12 of 5% for regimen or ribavirin comparisons and more than 80% power to detect absolute differences in SVR12 of 7% or more for the strategy comparisons.

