### Statistical analysis

The final analysis will estimate risk differences between groups using marginal effects after logistic regression. The model will include all main randomised effects and strata and will test interactions between all randomisations (Supplementary Methods, Additional file 1). Interactions will be included in the final model only if the 95% credible interval for the interaction term excludes no effect (*P* <0.05 for frequentist analyses). The interaction between regimen and strategy will include all levels of strategy. Owing to the partial factorial randomisation, the interaction between ribavirin and strategy will not include the standard treatment length strategy. Comparisons of regimens and of strategies will be non-inferiority analyses, and the ribavirin comparison will be a superiority analysis. Primary analysis will be intention-to-treat using Bayesian methods and 90% credible intervals. Secondary analyses will consider per-protocol populations, frequentist methods, and 95% credible and confidence intervals.

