### Power for final analysis

Given the lack of knowledge of the standard 12-week cure rates for this population (anticipated 50% of patients with genotype 6) and how cure rates in the shortened treatment with ribavirin groups will compare to these and to shortened treatment without ribavirin, there is uncertainty regarding the overall power for the final analysis even if the overall cure rate is 95% (Table 5). If we assume equality between regimens and a 5% absolute difference for ribavirin, then these constraints mean that the cure rates in each group are completely determined by the difference between the shortening strategies. Non-inferiority can exist between the standard duration group and the pooled shortening strategy groups, the shortening strategy without ribavirin groups, or the shortening strategy with ribavirin groups, meaning that the shortening strategy with ribavirin groups can have cure rates 2.5% higher than, 5% higher than or equal to the standard duration groups respectively. These alternatives are shown in different columns of Table 5.

**Table 5 Tab5:** Group-specific cure rates and power for 1092 patients with an overall 95% cure rate

	Ribavirin group cure rate compared with 12 week standard treatment cure rate		
	5% higher	2.5% higher	Equal
Group-specific cure rates:			
Standard 12-week treatment groups	93.3%	95%	96.7%
Shortened treatment with ribavirin groups	98.3%	97.5%	96.7%
Shortened treatment without ribavirin groups	93.3%	92.5%	91.7%
Power for a:			
5% non-inferiority margin for regimen comparison	99%	98%	97%
10% non-inferiority margin for strategy comparison	100%	100%	96%
5% absolute difference for ribavirin comparison	98%	95%	91%

Group-specific cure rates are such that overall cure rate in 1092 patients is 95%, ribavirin effect between shortened treatment groups is 5% and there is no effect of regimen. The effect of ribavirin in shortened treatment compared with standard treatment is varied to reflect uncertainties in the cure rates and to vary the no effect of strategy between standard treatment and shortened treatment without ribavirin, shortened treatment with ribavirin and pooled shortened treatment groups. Power is calculated with one-sided alpha of 0.05 for non-inferiority margins and two-sided alpha of 0.05 for superiority comparisons reflecting the design. Power assumes that no groups have been stopped during recruitment.

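### The 5% loss to follow-up that sizes the trial is left out of the comparison sizes and of every stated final-analysis power

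*Protocol article*

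**What the plan says.** All references are to the Protocol article.

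- **Sample size (Methods), sizing step.** The design tests "the null hypothesis that the true cure rate was 90% in each group compared with an alternative, unacceptably low, cure rate of 70"%, "given 90% power and one-sided alpha of 0.05", and adds an allowance for loss: "and 5% loss to follow-up by EOT + 12, 39 patients would be required per group". Multiplying up over groups and genotype strata, it arrives at "giving a total sample size of 1092 patients (39*14*2").
- **Sample size, comparison sizes.** "There will then be 546 per group for the regimen comparison", with 156 control v 312 per strategy, and 468 v 468 for ribavirin.
- **Sample size, power.** At a 95% overall cure rate, "the fixed total sample size of 1092 patients above provides 97% power to demonstrate non-inferiority between drug regimens" (5% margin). It also gives 96% for strategy non-inferiority (10% margin), and more than 90% for a 5% regimen or ribavirin difference.
- **Power for final analysis, Table 5.** "Group-specific cure rates are such that overall cure rate in 1092 patients is 95"%. The columns '5% higher', '2.5% higher' and 'Equal' give 99/98/97% for regimen, 100/100/96% for strategy and 98/95/91% for ribavirin. The only restriction stated is that no group has been stopped.
- **Statistical analysis.** "Primary analysis will be intention-to-treat using Bayesian methods and 90% credible intervals".
- **Primary endpoint.** Observed endpoints are classed as cure or failure. The article says nothing about a patient with no result 12 weeks after the end of treatment and no prior failure.

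**The concern.** The loss enters the calculation once, to turn the evaluable number per stratum into 39, and then drops out. If 5% of patients are expected to have no primary outcome, power for the final comparisons should not be quoted for 1092 observed outcomes.

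The point deserves a check because the expected loss (5%) is as large as the expected failure rate (100% − 95% = 5%). Leaving lost patients out costs a little precision. Counting them as non-cures roughly doubles the apparent failures, which raises the variance of every comparison and shrinks a true 5-point difference. The statement at stake is that power exceeds 90% for regimen, strategy and ribavirin whatever the control cure rate. It appears in the abstract and is largely repeated in the power section.

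**Working it through.** **1. Reproducing 39 and 1092.** Exact one-sample binomial, 70% v 90%, one-sided alpha 0.05. At n = 37, requiring at least 31 cures gives P(≥31 | 0.70) = 0.044 and P(≥31 | 0.90) = 0.929. With the hypotheses reversed (90% null, 70% alternative), power at n = 37 is 0.905. Then 37/0.95 = 38.95, so 39, and 39 × 14 × 2 = 1092. The 5% is therefore what moves 37 to 39.

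**2. Comparison sizes.** As printed, 546 + 546 = 1092, 156 + 3 × 312 = 1092, and 468 + 468 = 936 (all non-control patients). No one is removed. With 5% lost:
- 1092 × 0.95 = 1037.4, so about 55 outcomes are missing
- 546 × 0.95 = 518.7
- 156 × 0.95 = 148.2 and 312 × 0.95 = 296.4
- 468 × 0.95 = 444.6

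**3. Normal-approximation power.** Non-inferiority: power = Φ[(d + margin)/SE − 1.645], with SE = √(p1q1/n1 + p2q2/n2) and q = 1 − p. Superiority: power = Φ[(d − 1.96·SE0)/SE], with SE0 the pooled standard error. For lost = non-cure, all rates are multiplied by 0.95 and the full numbers are kept.

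*Regimen, 95% v 95%, margin 5%*
- All observed (546 per group): 0.05/0.01319 − 1.645 = 2.146, power 98.4% (printed 97%)
- Lost left out (519): 0.05/0.01353 − 1.645 = 2.051, power 98.0%
- Lost as non-cures (90.25%, 546): 0.05/0.01795 − 1.645 = 1.140, power 87.3%

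*Strategy, 'Equal' column, shortened (96.7 + 91.7)/2 = 94.2% v control 96.7%, margin 10%*
- 312 v 156: 0.075/0.01949 − 1.645 = 2.204, power 98.6% (printed 96%)
- 296 v 148: 0.075/0.02000 − 1.645 = 2.104, power 98.2%
- Lost as non-cures (d = −0.02375): 0.07625/0.02794 − 1.645 = 1.084, power 86.1%

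*Ribavirin, 'Equal' column, 96.7% v 91.7%*
- 468 per group: (0.05 − 1.96 × 0.01528)/0.01519 = 1.320, power 90.7% (printed 91%)
- 445 per group: (0.05 − 1.96 × 0.01567)/0.01558 = 1.238, power 89.2%
- Lost as non-cures (d = 0.0475): (0.0475 − 1.96 × 0.02005)/0.01999 = 0.410, power 65.9%

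**4. Simulation in the article's manner.** 5000 datasets per scenario, 14 groups, main-effects logistic model, marginal risk differences. Power in %, columns '5% higher' / '2.5% higher' / 'Equal':

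| Comparison | Table 5 | All 1092 observed | 5% left out | 5% scored as non-cures |
|---|---|---|---|---|
| Regimen, 5% margin | 99/98/97 | 99.0/98.6/97.7 | 98.2/97.9/97.4 | 88.3/88.2/86.0 |
| Strategy, 10% margin | 100/100/96 | 100/100/99.2 | 100/100/98.8 | 99.7/97.8/88.3 |
| Ribavirin, 5% difference | 98/95/91 | 97.9/95.0/91.3 | 97.3/93.9/90.3 | 72.4/69.2/67.4 |

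A second, separate simulation agreed:
- Ribavirin: 97.8/95.2/91.8 with all observed, 97.3/94.5/90.1 with lost left out, 67–73 with lost as non-cures.
- Regimen: 98.9/98.6/97.9, 98.8/98.2/97.2 and 87–88 in the same order.
- Strategy: about 98.6–100 with lost left out, and 87 in the 'Equal' column with lost as non-cures.

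The printed regimen and ribavirin powers match the no-loss column to within about a point. The printed 96% for strategy in the 'Equal' column is lower than any no-loss or lost-left-out figure found here, so it is conservative.

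The simulation error on a power near 90% is √(0.9 × 0.1/5000) = 0.4 points, so 90.1–90.3% cannot be told apart from 90%.

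**5. The 7-point strategy difference (more than 80% power).** The article gives no base rates. Assuming 97% v 90%, power is 80.7% with all observed, 78.4% with lost left out and 55% with lost as non-cures. With all observed it ranges from 70% (95% v 88%) to 87% (98% v 91%), so the base rate matters more here than the loss.

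**The case against.** The numbers 546, 156/312 and 468 are randomised allocations, and those are the right group sizes for an intention-to-treat analysis. The 5% loss belongs to a separate single-group calculation whose job was only to fix the total. When lost patients are left out, the non-inferiority powers stay at or within about a point of the printed values, and simulated ribavirin power still touches 90%. **This stands.** It is why a reader should not infer that the trial fails to deliver its stated power: under that scoring, only ribavirin in the 'Equal' column comes to its limit.

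The large falls need a missing = failure rule that the article does not state. Intention-to-treat fixes analysis by randomised group and does not by itself say how a missing outcome is scored. That rule may sit in the full protocol or the statistical analysis plan, so its absence here is no fault. **This also stands**, and the larger figures are therefore conditional.

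A reader might also infer that lost patients would inflate false stopping at the interim analyses. The text does not support that. The Monitoring section conditions on data observed so far, Table 3 counts observed failures among analysed patients, and Table 4 counts patients who have reached 12 weeks after treatment. A lost patient without virological failure is not an observed failure. With observed outcomes only, cumulative false stopping at a true cure rate of 90% stays at about 4–5%.

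The Limitations section says that power should remain acceptable even if some patients are excluded. That remark concerns stopped groups. Its reasoning about spare power carries over to non-inferiority with lost patients left out. It does not carry over to ribavirin in the 'Equal' column, where there is almost none to spare.

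**Conclusion.** The inconsistency holds: the plan assumes 5% loss to reach 1092, then states comparison sizes and power as if all 1092 outcomes were observed, and the only caveat in Table 5 concerns stopped groups.

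Its size depends on a scoring rule that the article does not give:
- **Lost patients left out:** regimen and strategy non-inferiority remain at about 97% or more, and ribavirin is about 97/94/90%.
- **Lost patients scored as non-cures:** ribavirin about 67–73%, regimen non-inferiority about 86–88%, strategy non-inferiority about 86–88% in the 'Equal' column. The statements of more than 90% would then not hold for those comparisons.

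Both sets assume loss equal across groups and unrelated to outcome, no stopped groups, and frequentist power as in the article. The point is minor, unless missing = failure is the rule in force, in which case the headline power statements need correcting.

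**What to change.** - Rerun the existing power simulation with 5% loss.
- In Sample size, label 546, 156/312 and 468 as randomised, and add the evaluable numbers: about 519 per regimen, 148 v 296, and 445 v 445.
- Restate the powers in Sample size and Table 5 under the scoring rule that the intention-to-treat analysis uses, and show the missing = non-cure power beside them.
- If missing = non-cure is the rule, also revise the statements of more than 90% power in the abstract and in Power for final analysis.

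The cost is one simulation rerun and a few changed figures. No extra patients, no change to the design or stopping boundary, and no missing-data rule needs to be written into the article.

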### Statistical analysis

The final analysis will estimate risk differences between groups using marginal effects after logistic regression. The model will include all main randomised effects and strata and will test interactions between all randomisations (Supplementary Methods, Additional file 1). Interactions will be included in the final model only if the 95% credible interval for the interaction term excludes no effect (*P* <0.05 for frequentist analyses). The interaction between regimen and strategy will include all levels of strategy. Owing to the partial factorial randomisation, the interaction between ribavirin and strategy will not include the standard treatment length strategy. Comparisons of regimens and of strategies will be non-inferiority analyses, and the ribavirin comparison will be a superiority analysis. Primary analysis will be intention-to-treat using Bayesian methods and 90% credible intervals. Secondary analyses will consider per-protocol populations, frequentist methods, and 95% credible and confidence intervals.

Analysis priors for the final analysis are listed in Table 2; these differ from the monitoring priors as the aim of monitoring is only to identify poorly performing groups and not to compare the randomly assigned groups. The control cure rate analysis prior is beta (4.75, 0.25), which has a mean of 0.95 and a variance derived as for the monitoring priors. This mean was derived from previous research into the trial drug regimens [28, 29]. Sensitivity analyses will use a range of informative priors reflecting plausible belief in the clinical community. Sceptical analysis prior distributions were chosen with means corresponding to the null hypothesis for each randomisation and enthusiastic analysis priors with means y greater than this, where y is the non-inferiority margin or absolute difference specified in the power calculations. The variances were arbitrarily set such that 90% of the prior distribution is within ± y around the mean to reflect the strength of the belief in the mean effect. Thus, for example, the risk difference for the drug regimen comparison has the sceptical analysis prior centred on −5% (the null hypothesis for the non-inferiority comparison) with 90% limits ± 5%, giving a 0.05 probability that the cure rate will be 10% worse and a 0.05 probability the cure rate will increase (i.e., be more than 0%) (sceptical priors in each direction will be used for the regimen comparisons). The enthusiastic analysis prior is centred on 0% with 90% limits ± 5%, giving a 0.05 probability that the cure rate will be 5% worse and a 0.05 probability that it will be 5% better with one regimen than the other.

**Table 2 Tab2:** Priors to be used in final analysis

	Primary analysis: uninformative	Sensitivity analyses	
		Sceptical	Enthusiastic
Control cure rate	Beta(4.75, 0.25)	Beta(4.75, 0.25)	Beta(4.75, 0.25)
Regimen comparison	N(0, 10,000)	N(−0.05, 0.009)	N(0, 0.009)
Strategy comparison	N(0, 10,000)	N(−0.1, 0.0036)	N(0, 0.0036)
Ribavirin comparison	N(0, 10,000)	N(0, 0.009)	N(0.05, 0.009)

The beta prior for the control cure rate has mean 0.95 and variance 0.008

The model will also be adjusted for genotype, which will have the prior N (0, 10,000) in all analyses

N(m,v) is the normal prior with mean m and variance v

To define the performance characteristics of the proposed stopping guideline, posterior probabilities of cure rates and the probability of stopping groups at each number of outcomes were calculated analytically using beta and binomial distributions respectively. Timings of interim analyses were determined by applying the probabilities of stopping groups to a projected recruitment schedule. The average probability of stopping a genuinely inferior group was estimated by integrating the probability of stopping a group with respect to the monitoring prior beta (4.5, 0.5) over cure rates between 60% and 90%. The lower bound was determined from previous studies testing strategies most similar to those in VIETNARMS which have reported cure rates of more than 90% with lower confidence interval bounds of more than 60% [6, 7]. In studies with cure rates of less than 60%, all patients received shortened therapies, regardless of their HCV VL, and did not receive adjunctive drugs [32, 33]; therefore, they were not considered relevant to this analysis, although power would be even greater to stop such a group. Cure rates above 90% were not considered since groups with these cure rates should not be stopped and so do not affect timing of the analyses. Simulations of 5000 datasets with outcomes taken from binomial distributions were used to determine the overall probability of stopping a group, the cumulative probability of stopping groups at specified analysis time points, and to estimate power after being analysed using marginal effects after logistic regressions with a model containing all randomised comparisons, as described above. Predictive probabilities (the probability of achieving a success at the end of the trial) were calculated analytically using the beta-binomial distribution in R 3.5.1. All other analyses were performed by using Stata version 15.1.

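### The primary analysis uses 90% credible intervals without exempting superiority comparisons, while power for those comparisons is stated at two-sided alpha 0.05

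*Protocol article*

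**What the plan says.** All references are to the protocol article.

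- **Statistical analysis**, type of comparison: "Comparisons of regimens and of strategies will be non-inferiority analyses, and the ribavirin comparison will be a superiority analysis".
- **Statistical analysis**, the next sentence, on interval level: "Primary analysis will be intention-to-treat using Bayesian methods and 90% credible intervals". It makes no exception for ribavirin.
- **Statistical analysis**, where the 95% level appears: "Secondary analyses will consider per-protocol populations, frequentist methods, and 95% credible and confidence intervals".
- **Statistical analysis**, interactions: a term is kept only when its 95% credible interval excludes no effect. The article gives P below 0.05 as the frequentist counterpart.
- **Sample size**: power is stated "For superiority comparisons (conducted for ribavirin and any comparison that meets non-inferiority above) and two-sided alpha of 0.05". The non-inferiority power in the same paragraph uses one-sided alpha of 0.05.
- **Power for final analysis**, note to Table 5: "Power is calculated with one-sided alpha of 0.05 for non-inferiority margins and two-sided alpha of 0.05 for superiority comparisons reflecting the design".
- **Table 2**: the primary prior for the ribavirin effect is N(0, 10,000), labelled uninformative.

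**The concern.** One interval level is applied to two kinds of question. For non-inferiority, comparing the lower 90% bound with the margin is the counterpart of a one-sided 0.05 test, which is what the design states. For superiority, the counterpart of two-sided 0.05 is a 95% interval, and the plan makes that interval secondary.

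Ribavirin is one of the trial's three randomised questions. The primary interval could exclude no effect while the secondary 95% interval includes it, and the plan does not say which decides. The same applies to regimen or strategy superiority tested after non-inferiority. There is also an oddity inside the section: an interaction must clear a 95% interval to enter the model, while the main ribavirin effect is presented at 90%.

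**Working it through.** **Inputs**

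- Group size (Sample size): "468 per group for the ribavirin comparison (superiority; comparing each treatment-shortening strategy with and without ribavirin".
- Effect (Table 5 note): "ribavirin effect between shortened treatment groups is 5% and there is no effect of regimen". Table 5 gives the cure-rate pairs 98.3 v 93.3%, 97.5 v 92.5% and 96.7 v 91.7%.
- Stated ribavirin power (Table 5): 98%, 95%, 91%.
- Critical values: 1.960 for two-sided 0.05 (95% interval) and 1.645 for two-sided 0.10 (90% interval).

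**Step 1. Reproduce the stated power.** Normal approximation, unpooled variance:

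SE = √{[p1(1 − p1) + p2(1 − p2)] / 468}, power = Φ(0.05/SE − critical value).

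For the Equal column: SE = √[(0.967 × 0.033 + 0.917 × 0.083)/468] = √(0.10802/468) = 0.0152, and 0.05/SE = 3.29. Power is Φ(3.29 − 1.96) = 90.8% at the 95% level and Φ(3.29 − 1.645) = 95.0% at the 90% level.

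| Table 5 column | Stated | At two-sided 0.05 | At two-sided 0.10 |
|---|---|---|---|
| 5% higher | 98% | 97.0% | 98.6% |
| 2.5% higher | 95% | 94.2% | 97.1% |
| Equal | 91% | 90.8% | 95.0% |

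The first column does not separate the two levels. The second is closer to 0.05, and the third fits 0.05 and misses 0.10 by about 4 points. Allowing 5% loss (0.95 × 468 = 444.6 per group), the Equal column gives 89.4% and 94.1%, so the conclusion is the same. Table 5 was therefore computed at two-sided 0.05, as its note says.

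**Step 2. False-positive rate if the primary interval is used as the test.** With no ribavirin effect and 468 per group, 400,000 simulated trials at each cure rate, Wald interval for the risk difference:

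| Common cure rate | 90% interval excludes zero | 95% interval excludes zero | 90% interval, one direction only |
|---|---|---|---|
| 95% | 10.3% | 5.0% | 5.1% |
| 94.2% | 10.2% | 5.1% | 5.1% |
| 90% | 10.0% | 5.0% | 5.0% |

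A simple Bayesian version (independent Beta(0.5, 0.5) priors, 95% cure rate, 3,000 trials) gives 8.9% for the 90% credible interval and 4.6% for the 95% one. The simulation error on 8.9% is √(0.089 × 0.911/3000) = 0.5 points. This is not the planned model, which adjusts for genotype and the other randomisations and puts a Beta(4.75, 0.25) prior on the control cure rate. It shows only that the rate about doubles with weak priors too.

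**Step 3. Where the two intervals disagree.** At a common cure rate of 95%, SE = √(2 × 0.95 × 0.05/468) = 0.0142. The 90% interval excludes zero once the observed difference exceeds 1.645 × 0.0142 = 2.3 points. The 95% interval needs 1.96 × 0.0142 = 2.8 points. Observed differences between about 2.3 and 2.8 points would give conflicting answers.

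**The case against.** The strongest objection is that the article gives an interval level, not a decision rule. The only Bayesian success criterion written out, under Limitations of the design, is the lower credible bound against the margin, and it concerns non-inferiority. A reader might infer that the ribavirin test is planned at two-sided 10%. The article does not say so, and it states two-sided 0.05 for superiority in two places. The 90% sentence may simply be a condensed statement written with non-inferiority in mind, and the Supplementary Methods or analysis plan, not shown here, may hold a separate threshold. This stands, and it makes the 10% figure conditional. It does not remove the conflict, because the printed sentence has no exception and assigns 95% to secondary analyses. The section's own interaction rule also treats an interval excluding no effect as the counterpart of a P value.

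Two further limits stand. A reader might take the superiority comparisons to have determined the sample size at 0.05. They did not: the Sample size section derives 1092 from a single-group test of 90% against 70%, and comparative power was assessed afterwards. And an exact 10% is not supportable under the planned Bayesian model; roughly double is.

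It is also fair that the 95% interval will be reported, so a result clear only at 90% would be visible. Visibility does not settle which interval carries the primary conclusion.

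**Conclusion.** The point holds as an inconsistency between the primary interval level and the alpha stated for superiority. It covers ribavirin and any regimen or strategy superiority test made after non-inferiority. The rough doubling found above rests on three assumptions: superiority is judged by whether the primary interval excludes no effect, the vague prior lets the credible interval behave much like a confidence interval, and no unseen document sets a different rule. The documents do not support the flat statement that the ribavirin test runs at 10%. The non-inferiority comparisons, the total of 1092 and the stated ribavirin power are not affected.

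**What to change.** In Statistical analysis, replace the single interval level with two:

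- 90% credible intervals, lower bound against the margin, for the regimen and strategy non-inferiority comparisons;
- 95% credible intervals as primary for the ribavirin comparison and for any superiority test made after non-inferiority, with superiority declared when the interval excludes no effect.

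If 90% is really intended for superiority, the alpha and power in the Sample size section and Table 5 should instead be restated at two-sided 0.10. Either way, settle it before comparative results are seen, so that nobody chooses between two intervals afterwards.

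The preferred change is one sentence. It needs no more patients and no new power calculation. The primary superiority interval becomes about 19% wider (1.960/1.645 = 1.19).

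### Table 2 prints prior variances of 0.009 for the regimen and ribavirin comparisons, where the stated rule gives 0.0009; as printed, those sensitivity analyses have almost no force

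*Protocol article*

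**What the plan says.** The Statistical analysis section fixes the spread of the sensitivity priors by a rule: "The variances were arbitrarily set such that 90% of the prior distribution is within ± y around the mean". It defines the half-width as follows: "where y is the non-inferiority margin or absolute difference specified in the power calculations".

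The Sample size section supplies y for each comparison:
- Regimen: "a smaller 5% margin is chosen for the drug comparisons".
- Strategy: "a greater non-inferiority margin (here 10%) is relevant to drug-shortening".
- Ribavirin: the superiority power statement refers to "absolute differences in SVR12 of 5% for regimen or ribavirin comparisons".

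The text then works through the regimen sceptical prior, centred at −5% with 90% limits 5 points either side, "giving a 0.05 probability that the cure rate will be 10% worse and a 0.05 probability the cure rate will increase". The regimen enthusiastic prior gets the same ±5-point limits around 0.

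Table 2 lists the priors for the final analysis:

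| Comparison | Sceptical | Enthusiastic |
|---|---|---|
| Regimen | N(−0.05, 0.009) | N(0, 0.009) |
| Strategy | N(−0.1, 0.0036) | N(0, 0.0036) |
| Ribavirin | N(0, 0.009) | N(0.05, 0.009) |

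The note beneath the table settles the notation: "N(m,v) is the normal prior with mean m and variance v".

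**The concern.** The text and Table 2 cannot both be right when y = 5%. The table is also out of order within itself. Halving y from 10% to 5% should divide the variance by four, yet the ±5% priors have a variance 2.5 times as large (0.009/0.0036) as the ±10% priors.

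A sceptical or enthusiastic prior is useful only if it is strong enough to move the result. If it is ten times too diffuse, the sensitivity analysis mostly repeats the uninformative one. The trial could then report that its regimen and ribavirin conclusions hold under plausible clinical scepticism or enthusiasm when neither had been tested at the stated strength. That affects two of the three randomised comparisons.

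**Working it through.** **Formula.** For a normal prior with 90% of its mass within ±y, SD = y/1.645 and variance = (y/1.645)².

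**Reproducing the strategy row (y = 0.10).** SD = 0.10/1.645 = 0.0608, so the variance is 0.0037. With the SD rounded to 0.06 it is 0.0036, exactly as printed. The rule is therefore the one used for this row.

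**Regimen and ribavirin rows (y = 0.05).** SD = 0.05/1.645 = 0.0304, so the variance is 0.00092. With the SD rounded to 0.03, as the strategy row suggests, it is 0.0009. The table prints 0.009, exactly 10 times the rounded value and 9.7 times the unrounded one.

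**What the printed value implies.** SD = √0.009 = 0.0949.
- 90% limits: 1.645 × 0.0949 = ±15.6 points.
- Each tail of the worked example (below −10%, or above 0): P(Z > 0.05/0.0949) = 0.30, against 0.05 in the text.
- Mass within ±5 points: 40%, against 90%.

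With 0.0009, the limits are ±4.9 points, each tail is 0.048 and 90.4% lies within ±5 points. This agrees with the text.

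**Other readings of 0.009.** Treating ±5% as 80% limits gives a variance of 0.0015, and as 95% limits 0.00065. Reading 0.009 as an SD would put more than 99.99% of the prior within ±5 points. None of these gives the printed figure.

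**Effect on the posterior.** I used a conjugate normal approximation on the risk-difference scale: prior weight = SE²/(SE² + v), where v is the prior variance.
- Regimen: 546 per group (Sample size) and 95% cure in both (Sample size). SE = √(2 × 0.95 × 0.05/546) = 0.0132.
- Ribavirin: 468 per group (Sample size) and cure rates of 97.5% and 92.5% (middle column of Table 5). SE = √((0.975 × 0.025 + 0.925 × 0.075)/468) = 0.0142.

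| | v = 0.009 | v = 0.0009 |
|---|---|---|
| Regimen prior weight | 1.9% | 16.2% |
| Regimen prior, equivalent patients per group (2 × 0.0475/v) | 11 | 106 |
| Regimen sceptical posterior mean, observed difference 0 | −0.10 points | −0.81 points |
| Regimen sceptical lower 90% bound, observed difference 0 (flat prior: −2.17 points) | −2.24 points | −2.80 points |
| Ribavirin prior weight | 2.2% | 18.2% |
| Ribavirin shrinkage under sceptical prior, observed difference 5 points | 0.11 points | 0.91 points |
| Ribavirin sceptical lower 90% bound, observed difference 2.5 points | +0.14 points | −0.06 points |

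In the last row the sceptical conclusion changes with the variance. Using 0.00092 in place of 0.0009 gives weights of 15.8% and 17.8%.

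**The case against.** The discrepancy itself is hard to dispute; the argument is about how much it matters.

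- **Only sensitivity analyses are touched.** The primary analysis uses N(0, 10,000) throughout. Sample size, power, the stopping guideline and interim timing do not use these cells. This stands.
- **The strategy comparison is sound.** It carries the treatment-shortening question, its priors are correct, and its sceptical prior has about 11% weight by the same approximation. This also stands, and the point is confined to regimen and ribavirin.
- **The intended prior is described in words beside the table.** A careful analyst could recover it. The article cannot show whether 0.009 was programmed or is only a misprint, and the Supplementary Methods it cites were not available here. The harm is therefore conditional on the table being coded as printed. That is a real possibility, because the table is the list of priors for the final analysis.
- **Few decisions would flip under the sceptical priors.** In the same approximation with 90% intervals, regimen non-inferiority needs an observed difference above −2.81 points with 0.009 and above −2.63 with 0.0009. Ribavirin superiority needs 2.35 and 2.57 points respectively. Each window is about 0.2 points wide. For the enthusiastic priors the windows are about 0.7 points (regimen) and 0.8 points (ribavirin). So many results would lead to the same conclusion either way, but not all, and the reported estimates and bounds would differ throughout.
- **The weights are approximate.** The planned model is a logistic regression with marginal effects, so they are indicative. The tenfold error in the variance does not depend on them.

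**Conclusion.** The concern holds. Four cells of Table 2 contradict the rule and the worked example in the same section by a factor of ten, and no alternative reading gives the printed figure. Three things in the article point to 0.0009: the rule, the 0.05 tail probabilities and the strategy row.

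If the table is followed as printed, the regimen and ribavirin sensitivity priors carry about 2% of the posterior weight instead of 16% to 18%. The sceptical and enthusiastic posterior means, whose prior means are 5 points apart, then differ by only about 0.1 points (0.019 × 5 for regimen, 0.022 × 5 for ribavirin) instead of 0.8 to 0.9. These figures assume full recruitment with no stopped groups or losses, the article's cure rates, and the normal approximation.

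The primary results do not change. The correction is still needed, because analysts cannot follow both text and table, and the choice should not be left until data are seen.

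**What to change.** In Table 2, replace 0.009 with 0.0009 in all four cells:
- Regimen: N(−0.05, 0.0009) sceptical and N(0, 0.0009) enthusiastic.
- Ribavirin: N(0, 0.0009) sceptical and N(0.05, 0.0009) enthusiastic.

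Use the same variance for the sceptical regimen prior in the opposite direction, which the text mentions but the table does not list. Leave the strategy row as it is. Check that the statistical analysis plan and any existing analysis code carry the corrected value. The cost is four table entries and a code check; no design feature, sample size or primary analysis changes.
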